### Sample size calculation

The sample size will be calculated using PASS 15.0.5 based on the means, standard deviations and an alpha of 5% (0.05) with a unilateral contrast. Assuming that the standard deviation of NDI scores is 8, then 38 participants per group will give the study 80% power to detect minimum clinically important differences (MCID) of 5 units in NDI [34]. Meanwhile, 41 participants per group are required based on the 10 cm VAS scale with a standard deviation of 5 and a clinically significant difference of 3 points [26]. To accommodate an expected dropout rate of 20% during follow-up and to have sufficient statistical power for the different variables in this study, a total of 150 participants will be sufficient.

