### Statistical analysis

The statistical analysis will be carried out using the IBM SPSS Statistics 26 software. Descriptive statistics will be used to describe the study population and will be summarised per group based on the number of observations, means and standard deviations. The primary and secondary outcome variables (VAS, NDI, CROM, PPT and GPE) will be analysed by intention to treat and by using linear mixed models with repeated measures. The linear mixed model requires the residuals to be normally distributed. The Shapiro–Wilk test will be applied to test the normality. In case of a non-normal distribution of the residuals, an appropriate non-parametric test will be conducted. Multiple post-hoc comparisons will be conducted through Bonferroni’s contrast for parametric distributions. All tests will be two sided, and the level of significance is set to 0.05. The missing data in this study will be handled with a mean imputation or mixed modelling approach.

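### The protocol allows mean imputation of missing data; if it is used for outcome scores it either understates the standard error or shrinks the effect, and the planned mixed model makes it unnecessary

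*Protocol article*

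**What the plan says.** Under Statistical analysis, the primary and secondary outcomes (VAS, NDI, CROM, PPT and GPE) "will be analysed by intention to treat and by using linear mixed models with repeated measures". The section closes with: "The missing data in this study will be handled with a mean imputation or mixed modelling approach". It does not say which of the two applies, to which variables or visits, or whether the mean is that of the arm, of all participants or of the participant's own other values. It also states: "All tests will be two sided, and the level of significance is set to 0.05".

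The Sample size calculation section adds participants "To accommodate an expected dropout rate of 20% during follow-up" and arrives at 150 in total. The Randomisation section splits these equally over three groups. The Abstract (Methods) says that group-by-time differences will be analysed with linear mixed models, with assessments at baseline, week 4 and week 12.

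**The concern.** Single mean imputation enters made-up values into the analysis as if they had been observed. If the arm mean is used, the added values have no spread and the sample looks larger than it is, so confidence intervals are too narrow and p-values too small. If the overall mean is used, each arm is pulled towards the others and the effect is understated.

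The protocol itself writes this method in as a permitted route, and the sentence could be applied to the two primary outcomes. It is therefore not a detail merely left for an analysis plan to supply. The two routes can also give different answers from the same data, and the sentence contains no rule for choosing between them. At stake are the error rate of the main comparisons and the estimated size of the benefit.

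**Working it through.** **Inputs from the protocol**
- Total 150 in three equal arms, so n = 50 per arm. The total follows from the larger per-group figure: 41 × 1.2 = 49.2, rounded up to 50, and 50 × 3 = 150.
- Dropout d = 0.20, so 10 of 50 are missing and 40 observed per arm.
- NDI: "Assuming that the standard deviation of NDI scores is 8"; the difference of interest is 5 points.
- Two-sided alpha 0.05.

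**Assumptions that are not in the protocol**
- Data are missing completely at random.
- The fill is applied to whole outcome scores at the follow-up visit, with baseline complete.
- Two-arm comparisons (t test, change score, baseline-adjusted) stand in for the mixed-model contrasts.

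**Reference: observed data, no imputation**
SE = 8 × √(2/40) = 1.79. Simulation of 40,000 trials gave a mean reported SE of 1.78, type I error 5.0% and estimate 5.0.

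**Arm-mean fill, single-visit comparison**
- Reported variance of an arm mean: (39/49) × σ²/50. True variance: σ²/40.
- SE ratio = √[(39/49) × 40/50] = √0.637 = 0.80, so the SE is about 20% too small.
- In NDI points: reported 8 × √[(2/50) × (39/49)] = 1.43 (1.42 in simulation) against a true 1.79.
- Type I error ≈ 2 × [1 − Φ(1.96 × 0.80)] = 2 × [1 − Φ(1.568)] ≈ 11.7%. Simulation gave 11.8%.
- With baseline adjustment, simulation (20,000 trials, baseline correlation 0.3, 0.5, 0.7) gave about 11.8–11.9%.

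**Arm-mean fill, change from baseline (group-by-time contrast)**
Let ρ be the correlation between baseline and follow-up, with equal variances σ². Ignoring small-sample terms:
- Reported variance of the mean change: σ²[(1−d) × 2(1−ρ) + d]/n = σ²[2 − d − 2ρ(1−d)]/n.
- True variance: σ²[1/(1−d) + 1 − 2ρ]/n = σ²[2 − d − 2ρ(1−d)]/[(1−d)n].
- The variance ratio is 1 − d whatever ρ is, so the SE ratio is √0.80 = 0.894, about 10.6% too small.
- Type I error ≈ 2 × [1 − Φ(1.96 × 0.894)] ≈ 8.0%. Simulation gave 7.7–7.9% for ρ from 0.3 to 0.7, with the SE about 11% too small.

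**Overall-mean fill**
Each arm's mean becomes 0.8 × (observed arm mean) + 0.2 × (overall mean). The last term cancels between arms, so the difference is multiplied by 0.8: 5 × 0.8 = 4.0. Simulation gave 4.0. In the single-visit test the type I error stayed near 5% (5.1%).

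**Sensitivity to the amount missing (simulation, except where marked as formula)**

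| Missing | Arm mean: type I, single visit | Arm mean: type I, change (formula) | Overall mean: 5 points estimated as |
|---|---|---|---|
| 10% | 7.5% | 6.3% | 4.5 |
| 20% | 11.8% | 8.0% | 4.0 |
| 30% | 17.5% | 10.1% | 3.5 |

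**The case against.** The strongest reply is that the article already contains a sound route. It commits the outcomes to intention-to-treat mixed models and names mixed modelling as one way to handle missing data. The sentence speaks of missing data in general, so it could also cover baseline variables or single unanswered NDI items, where a mean fill matters far less. Dropout of 20% refers to the whole follow-up, so fewer scores should normally be missing at week 4. All of this stands. It makes the harm conditional, but it does not make mean imputation acceptable for outcome scores, and the sentence does not exclude that use.

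Three stronger readings are tempting but not supported:
- A reader might infer that the false-positive rate would more than double. That holds for a single-visit or baseline-adjusted comparison. For the group-by-time contrast named in the Abstract it is about 8%. The article does not fix the contrast closely enough to choose one figure, so a range is the honest statement.
- A reader might infer that the method will be picked once results are known. The wording leaves room for that, but an analysis plan that is not shown may settle the choice.
- A reader might count the lack of a missing-not-at-random sensitivity analysis as a fault. That is commonly left to the analysis plan and is no defect of this article.

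**Conclusion.** The point holds in conditional form. The protocol permits an unsound way of handling missing data beside a sound one. The two harms are alternatives, not additive: which one occurs depends on which mean is meant, and the article does not say. A mean taken over the participant's own other values was not quantified.

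The sizes rest on 50 per arm, 20% of outcome scores missing at the visit analysed, missing completely at random, and simple two-arm contrasts in place of the full repeated-measures model. The exact figures in the fitted model will differ somewhat. For the arm mean and the overall mean, the direction will not. Nothing here shows that the trial's main analysis will use mean imputation, or that its results will be invalid.

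**What to change.** In the last sentence of Statistical analysis, delete the words *mean imputation or*. State instead that the primary analysis is the linear mixed model fitted by likelihood to all observed visits of all randomised participants, valid under missing at random, with no single imputation of outcome scores. If a mean fill is intended only for baseline variables or single questionnaire items, say so and give the rule.

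The cost is one sentence. Design, sample size and trial conduct are unaffected. A sensitivity analysis for outcomes missing not at random would be a reasonable optional addition, and can sit in the analysis plan.

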## Discussion

A previous pilot study reported that a computerised 3D cervical mobilisation device can be safely administered to patients with chronic neck pain. Using a small sample, this pilot study reported that such device can effectively alleviate neck pain and increase CROM [20]. Another preliminary trial investigating the physiological effect of computerised mobilisation reported a positive change in neck posture and cervical neuromuscular control for neck pain after the use of computerised mobilisation. However, neither of these studies compared the effects of computerised mobilisation and manual therapy on chronic neck pain [18]. To fill this gap, the present protocol describes the methods for a randomised controlled trial to compare the effectiveness of these techniques. Results of this study can help lighten the workload of therapists.

This article proposes two types of treatments, namely, manual therapy (mainly joint mobilisation and muscle stretching) and machine-assisted mobilisation based on the symptoms of neck pain. By observing how these two therapies reduce pain and improve functional ability, this article investigates whether Occiflex could be an alternative method that is possibly effective for treating neck pain. A control group with only home exercise and patient education will be added for comparison to understand the addition effect of mobilisation treatment and to gain a better understanding of the mechanism for WRNP. Computerised mobilisation is assumed to be superior to manual therapy and can generate more effects than exercise alone. The study contributes to the development of an evidence-based computerised therapy that can improve the therapeutic techniques being used in this field of clinical practice.

## Data Availability

Data sharing is not applicable to this article as no datasets will be generated or analysed in this study.

## Abbreviations

ANOVA: Analysis of variance
CCF: Cranio-cervical flexion
CROM: Cervical range of motion
GPE: Global perceived effect
ICC: Intraclass correlation coefficients
IPAQ: International physical activity questionnaire
MCID: Minimum clinically important differences
NDI: Neck disability index
PPT: Pressure pain threshold
HE: Home exercise
VAS: Visual analogue scale
WRNP: Work-related neck pain
